| --- |
| **6- Objectives:**  This study aims to investigate, on mechanism-based, the possible therapeutic effects of rosuvastatin when combined with androgen deprivation in metastatic prostate cancer patients. |
| **7- Study Design :**  Prospective study, a patient cohort will be selected according to the following criteria (According to the institutional review board of the NCI): Newly diagnosed cancer prostate patients over 50 years old who will be under primary intervention with surgical castration. Statin will be used at the time of castration. Patients will be classified into two groups treated with castration with or without Rosuvastatin 20 mg/day. |
| **8- Study Methodology:**   1. Population of study &disease Condition   A cohort of 80 patients will be selected according to the following criteria (According to the institutional review board of the NCI): Newly diagnosed cancer prostate patients over 50 years old who will be under primary intervention surgical castration. Statin will be used at the time of castration. Patients will be classified into two groups treated with castration with or without Statin. Using power 85% and 5% significance level, 35 patients are required. |
| b) Back ground and Demographic characteristics   - Male - Over 50 year old   Metastatic prostate cancer |
| c) Inclusion criteria:  Naïve newly diagnosed with metastatic prostate cancer  ▪ Age ≥ 50 years.  ▪ No psychological or geographical barriers for regular follow up of the patients. |
| d) Exclusion criteria:  ▪ Age < 50 years.  ▪ psychological or geographical barriers for regular follow up of the patients. |

| e) Interventions:  Rosuvastatin 20 mg/day for 6 months will be administered at the time of castration | |
| --- | --- |
| f) Possible Risk: **No** drug interaction |  |
| g) Primary outcome parameter   - Lipid profile and metabolism markers: LDL, cholesterol, triglycerides, HDL, HMG-CoA reductase, ABCA1 , SLDLRP1, AKR1C4. - Tumor aggressiveness markers: PSA, ALP, Caveolin-1, EGFR |  |
| h) Secondary outcome parameters:  Short term clinical outcome in terms of disease progression/regression and overall survival |  |
| i) Sample size  A cohort of 80 patients will be selected according to the following criteria (According to the institutional review board of the NCI). Patients will be classified into two groups treated with surgical castration with or without Statin. |  |

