| j) Statistical analysis:  Randomization, data management and statistical analysis were performed using The Statistical Package for Social Sciences (SPSS) version 24. Normal distribution and variance homogeneity of data were assessed using the Kolmogorov–Smirnov and Levene’s tests, respectively.  Numerical data were summarized using median and interquartile range (IQR). Categorical data were summarized as count and percentage. Patients were stratified according to their clinicopathological factors and for more than two subgroups of patients, the change in measured parameters were tested for significance using Kruskal–Wallis test and the pairwise comparison were done using Mann–Whitney. The change in proteins concentration over time was tested using Friedman test of significance. Spearman correlation analysis was used to test all possible correlations. Kaplan- Meier survival analysis was used to calculate the cumulative survival rate as well as median levels of OS after two years of follow up. OS was calculated from date of diagnosis to date of death by any cause. Living patients or patients lost to follow-up were censored on the last known alive date. The hazardous effect of death or progression Cox proportion hazard Model was used to evaluate the hazardous effect of different clinicopathological and proteins levels on death and progression. All P-values are two-sided. P-values < 0.05 were considered significant. Patients were equally allocated between the two study arms, but ten patients from the control group lost follow-up and were excluded from all tests. |  |
| k) Source of funding: Cairo University |  |

| **9-Ethical committee approval:**  The study ID BB1901-30303 was approved by the Institutional Human Research Ethics Committee of NCI, Egypt, Number 00004025, with IRB review Number 201819019.3 |
| --- |
| **10- Cooperation with other departments:**  Name of department : Medical Oncology  Name of investigator: [name]  Name of department : Surgical Oncology  Name of investigator: [name]  Name of department : Biostatistics and Cancer Epidemiology  Name of investigator: [name] |

1. [] Ferlay J, Ervik M, Lam F, Colombet M, Mery L, Piñeros M, et al. Global cancer observatory: cancer today. International Agency for Research on Cancer, Lyon, France, 2018. <https://gco.iarc.fr/today>  [↑](#endnote-ref-1)

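### The stated survival methods do not compare the two arms, and ten lost controls are excluded despite the protocol's own censoring rule

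*Protocol*

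**What the plan says.** Section 6 gives the aim as "the possible therapeutic effects of rosuvastatin when combined with androgen deprivation in metastatic prostate cancer patients". Section 7 sets up the comparison: "Patients will be classified into two groups treated with castration with or without Rosuvastatin 20 mg/day". Section 8 h) names the secondary outcomes: "Short term clinical outcome in terms of disease progression/regression and overall survival".

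Section 8 j) then writes out the survival methods.

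- Kaplan-Meier is used for the cumulative survival rate and "median levels of OS after two years of follow up". The groups for which these are calculated are not named.
- The regression is described as "Cox proportion hazard Model was used to evaluate the hazardous effect of different clinicopathological and proteins levels on death and progression".
- OS starts at diagnosis. Patients who are alive or lost to follow-up are censored when last known alive.
- The closing sentence says that allocation was equal, but that ten controls were lost to follow-up and left out of all tests.

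No log-rank test, arm term or hazard ratio for rosuvastatin appears anywhere in the protocol.

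**The concern.** The question posed is whether rosuvastatin changes progression or survival. The analysis stated asks which patient characteristics and protein levels go with death or progression. That is a prognostic question, and answering it gives no treatment effect.

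The handling of losses adds a second problem. A patient lost to follow-up has by definition been followed alive for some time. Censoring keeps that time at risk, and exclusion discards it. Here it is discarded in the control arm. Compared with censoring, removing death-free follow-up from the control arm alone can only raise the estimated control death rate, or leave it unchanged if the ten had no follow-up. For OS, any shift therefore favours rosuvastatin.

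**Working it through.** **1. Text against text.** The outcomes in section 8 h) are set beside the methods in section 8 j).

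- OS: Kaplan-Meier rate and median; Cox on clinicopathological factors and protein levels. No arm comparison stated.
- Progression: Cox on the same factors. No arm comparison stated.
- The Mann-Whitney, Kruskal-Wallis and Friedman tests in section 8 j) concern measured parameters and protein concentrations, not censored times, so they do not fill the gap.

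**2. The plan's own sample-size figure.** Section 8 a) states: "Using power 85% and 5% significance level, 35 patients are required". It gives no endpoint, effect size or standard deviation, so the 35 cannot be reproduced. With k = 1.960 + 1.036 = 2.996 and k² = 8.978, back-solving for a difference in means gives:

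- 35 per arm: d = √(2 × 8.978 / 35) = 0.716
- 35 in total: d = √(4 × 8.978 / 35) = 1.013

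Neither is a survival calculation, so the plan has no stated power for OS or progression.

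**3. Numbers analysed.** The cohort is 80 ("A cohort of 80 patients will be selected according to the following criteria") with equal allocation, hence 40 v 40. Dropping ten controls leaves 40 v 30 = 70, and 10/40 = 25% of the control arm is removed. If a proportion q of the 30 kept controls die within two years, the proportion among all 40 lies between 0.75q (none of the ten died) and 0.75q + 0.25 (all ten died). That range is 25 percentage points wide whatever q is.

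**4. What an arm comparison could show.** The inputs are 85% power and 5% from section 8 a), and "All P-values are two-sided" from section 8 j). The hazard ratios are assumptions, because the protocol gives none. By Schoenfeld's formula, deaths needed = k² / [p(1 − p)(ln HR)²], with p = 40/70 and p(1 − p) = 0.2449.

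- HR 0.5: 8.978 / (0.2449 × 0.4805) = 76.3, so 77
- HR 0.6: 8.978 / (0.2449 × 0.2609) = 140.5, so 141
- HR 0.7: 8.978 / (0.2449 × 0.1272) = 288.2, so 289

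Each exceeds 70. With 1:1 allocation, HR 0.5 needs 75 deaths by Schoenfeld or 81 by Freedman. Keeping all 80 patients would therefore still require almost all of them to die.

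The protocol states no death count. Power for HR 0.5 at 40 v 30 under assumed counts is:

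| Deaths among 70 | Power |
|---|---|
| 14 (20%) | 25% |
| 28 (40%) | 44% |
| 35 (50%) | 53% |
| 49 (70%) | 67% |

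**5. The marker models.** Section 8 g) lists 8 lipid and metabolism markers and 4 tumour markers, 12 in all.

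- If all 12 were modelled jointly, deaths per marker would be 14/12 = 1.2, 35/12 = 2.9 or 49/12 = 4.1, and 70/12 = 5.8 if every analysed patient died.
- Counting only 8 proteins (without LDL, cholesterol, triglycerides and HDL), the ceiling is 70/8 = 8.75.
- Both ceilings are below the usual rule of thumb of 10, before any clinicopathological factor is added.
- If each marker were tested singly at 0.05, the chance of at least one false positive is 1 − 0.95¹² = 46% for 12 independent tests, and 1 − 0.95²⁴ = 71% for 24 (death and progression).

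**The case against.** **This is detail for the statistical analysis plan.** That plan is not shown, the protocol does not say that survival is pooled over arms, and the clinicopathological factors are an open list to which arm might be added. It is therefore too strong to say that the comparison will never be made. What stands is that section 8 j) is not silent. It fixes the methods, time origin, censoring rule, types of covariate and significance level, and what it fixes answers a different question from the one in sections 6 and 8 h).

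**The median.** A reader might infer that median OS cannot be estimated if fewer than half the patients die within two years. The documents do not support this. Kaplan-Meier also yields the survival rate, and overall mortality below 50% does not keep both arms below it: 12/40 (30%) and 18/30 (60%) make 30/70 (43%) overall, yet one arm passes its median. Section 5 also says that most patients with relapsed or metastatic disease after castration die within two years, though this may describe a later disease state than that of newly diagnosed patients.

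**Overfitting.** A reader might infer that the Cox models are overfitted. The protocol does not say that covariates enter together. With one marker per model the issue is multiplicity instead.

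**Immortal-time and mediator bias.** The Friedman test shows that proteins are measured repeatedly, but no visit is named for Cox. If baseline values are used, neither bias arises. If on-treatment values enter as fixed covariates, both are possible.

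**Keeping all 80 patients.** Nothing shows that a date last known alive exists for each of the ten lost controls. This limits the remedy but does not resolve the contradiction.

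**Conclusion.** The point holds in this form: the survival analysis as stated specifies no comparison of arms for OS or progression, so it does not estimate rosuvastatin's effect on the secondary outcomes. In addition, the exclusion of ten lost controls contradicts the censoring rule in the same section and removes a quarter of one arm. Both conclusions rest on the protocol text alone and need no assumed event rate.

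An added comparison would be imprecise. About 77 deaths are needed for HR 0.5 at 85% power with 40 v 30, against 70 patients analysed. This rests on proportional hazards and an assumed HR, and smaller effects need far more deaths.

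The concerns about the marker models are conditional: on a joint model for too few events per covariate, on single testing for multiplicity, and on post-baseline values for survival-to-measurement and mediator bias. They are reasons to state the choice, not established errors. The matter should be corrected, but it concerns secondary outcomes.

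**What to change.** In section 8 j):

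- State that OS and progression are compared between arms by Kaplan-Meier with a log-rank test and by a Cox model with arm as the main term. Report the HR with 95% CI and two-year survival by arm.
- Include all allocated patients, censor those lost to follow-up at the date last known alive where one exists, and remove the exclusion of the ten controls from these analyses. Report how many of the ten have no usable date.
- Present the result as an estimate with its interval, not as a powered test.
- For Cox models of markers, state that baseline levels are used (or a landmark if on-treatment levels are wanted), include arm, limit the covariates to what the number of events supports, and label the results exploratory.

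The section is written in the past tense and already reports losses, so the comparison should be dated as an addition and not described as planned from the outset.

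The cost is mainly wording and a short re-analysis, plus retrieving last-contact dates for ten patients. Fewer multivariable predictors can be reported.

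### Section 8(j) as written post-dates follow-up, so it is not evidence of prespecification, and its exclusion of ten lost controls is post hoc and contradicts its own censoring rule

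*Protocol*

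**What the plan says.** Protocol section 8(j), Statistical analysis, opens in the past tense: "Randomization, data management and statistical analysis were performed using The Statistical Package for Social Sciences (SPSS) version 24". It goes on to report the checks of normality and equal variance as completed. It closes with what happened to the patients: "Patients were equally allocated between the two study arms, but ten patients from the control group lost follow-up and were excluded from all tests". No loss is mentioned for the rosuvastatin arm.

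The same section defines overall survival from diagnosis to death from any cause. It says that men still alive, and men lost to follow-up, are censored on the date they were last known to be alive.

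The decision rule is "P-values < 0.05 were considered significant", with "All P-values are two-sided". It is attached to no particular analysis. It therefore covers the primary markers in 8(g), the subgroup comparisons, every possible correlation, and the survival and Cox analyses.

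Sections 7, 8(a), 8(e) and 8(i) look forward, for example "A cohort of 80 patients will be selected according to the following criteria". Section 8(a) also gives the significance level: "Using power 85% and 5% significance level, 35 patients are required".

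**The concern.** A protocol is normally read as the record of what was fixed before the data. Section 8(j) sits where that record should be, but it contains an arm-specific count of losses that nobody could have known in advance. A reader who takes it as the plan would credit the tests and the analysis set with a prespecified status that this text cannot give them.

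Two things are at stake. First, a 5% threshold has its stated error rate only if the test, the scale and the analysis set did not depend on the results. Second, the analysis set described here leaves out men from one arm only, because of something that happened after allocation. For survival, that conflicts with the rule given a few lines earlier.

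**Working it through.** **1. Dating the text.** Sections 7, 8(a), 8(e) and 8(i) describe selection, grouping and treatment as still to come. Section 8(j) describes randomisation and analysis as done and gives the number lost in the control arm. These cannot have been written at the same time, so 8(j) was written or revised after the losses were known. By its own wording, this was also after analysis. The section carries no version or date.

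**2. Size of the exclusion.** Inputs are 80 patients (8(a), 8(i)), equal allocation and ten control losses (8(j)). It is assumed that all 80 were enrolled.
- Per arm: 80/2 = 40.
- Control loss: 10/40 = 25%. Rosuvastatin loss: none stated. Overall: 10/80 = 12.5%.
- Analysed: 40 rosuvastatin v 40 - 10 = 30 control.

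**3. The two rules for lost patients.**
- Censoring rule: a man lost to follow-up stays in the survival analysis until last known alive.
- Exclusion sentence: "ten patients from the control group lost follow-up and were excluded from all tests".

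For survival, both cannot apply to the same ten men. A general rule to drop lost patients could in principle be set in advance, but the document contains none. Its only general rule is censoring.

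The direction of the effect on the survival curve can be shown. The Kaplan-Meier estimate is the product of (1 - d/n) over death times, with d deaths among n at risk. Men lost while alive add to n but not to d. Removing them leaves d unchanged and lowers n, so the control curve falls or stays the same. For example, a single death while all ten would still be at risk gives 1 - 1/40 = 0.975 with them and 1 - 1/30 = 0.967 without them. The full effect cannot be calculated, because the dates of loss are not given.

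**4. Exposure if the analysis were free to vary.** The documents give no marker distributions, so these inputs are assumptions: log-normal baseline and follow-up values, log-SD 0.3 to 1.2, baseline-to-follow-up correlation 0.5 to 0.8, no drug effect, 40 v 30, and 4000 simulated trials per setting. Five ordinary analyses of one marker were compared: rank test on change, t test on change, rank test on ratio, t test on log ratio, and rank test on final value.
- One fixed Mann-Whitney test on change: P < 0.05 in about 5% of trials.
- Smallest P of the five: below 0.05 in about 10-14%.
- Smaller P of the two rank tests on change or final value: below 0.05 in roughly 9-10%.

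The t tests and the ratio scale are not named in 8(j), so the last figure is closer to the methods that section describes.

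**5. What is prospective.** The 5% level appears in 8(a), within the forward-looking part. The threshold therefore does not depend on 8(j).

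**The case against.** The strongest reply is that tense dates the text and not the decisions behind it. Section 9 refers to an ethics approval, and a separate SAP may exist. Either could contain the same tests, fixed in advance. Rank tests with medians and interquartile ranges are a natural advance choice for skewed markers. The aim in section 6 is to investigate possible effects, and the word confirmatory appears nowhere. A P < 0.05 statement is a convention, not a claim of confirmatory status.

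Most of this stands, and it rules out three stronger readings.
- A reader might infer that no test in 8(j) could ever support a confirmatory claim. That does not follow, because a dated earlier text could show that the tests came first.
- A reader might infer that the rank tests were chosen after the distributions were inspected. Section 8(j) reports the checks, but states neither their results nor any rule linking them to the choice of test.
- A reader might infer that the significance level was set after the data. Section 8(a) states it prospectively.

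The reply does not reach the exclusion of the ten controls. That sentence rests on an observed event and conflicts with the only general rule the document gives for lost patients. Nor does the reply make 8(j) evidence of prespecification. It says only that such evidence may exist elsewhere.

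**Conclusion.** The point holds in this limited form. Section 8(j) as it stands was written after follow-up, so it does not show that its tests were prespecified. Its analysis set, 40 v 30 after dropping a quarter of the controls, is post hoc and contradicts the section's own censoring rule. The 40 v 30 figure assumes that all 80 men were enrolled and that no rosuvastatin patient was lost.

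The exposure is a false-positive rate of about 10-14% per marker instead of 5% if the analysis was chosen freely among five options. It is roughly 9-10% if the choice lay only between two rank tests. Both figures rest on assumed distributions. They show what is possible when choices are not fixed, and they do not show that any choice was driven by the data. Unless a dated earlier text shows otherwise, the results should be read as exploratory.

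**What to change.** 1. Give 8(j) a version and a date, and state that it was written after follow-up.
2. Label the exclusion of the ten controls as a post hoc decision and reconcile it with the censoring rule, so that these men contribute to overall survival up to the date last known alive.
3. Keep the P < 0.05 significance wording only for analyses that a dated earlier protocol version or SAP shows were fixed before the data.
4. Report all other marker, subgroup, correlation and survival results as exploratory, as estimates with 95% confidence intervals.

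The cost is rewording, a short version history and a rerun of the survival analysis with the ten men included. The downside is that some conclusions become exploratory.

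### Ten control patients lost to follow-up are dropped from every test, against the section's own censoring rule for overall survival, leaving a completer comparison with exclusions reported in the control arm only

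*Protocol*

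**What the plan says.** Section 8(i) of the protocol plans 80 patients: "A cohort of 80 patients will be selected according to the following criteria". They form two groups, castration with or without the statin. Section 8(j) mentions randomization and adds that "Patients were equally allocated between the two study arms".

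On patients lost to follow-up, section 8(j) makes two statements:

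- Directly after defining OS, which it counts from diagnosis until the patient dies of whatever cause, it sets this rule: "Living patients or patients lost to follow-up were censored on the last known alive date".
- In its last sentence: "ten patients from the control group lost follow-up and were excluded from all tests".

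The tests in that section include Kaplan-Meier estimates of OS after two years of follow-up, Cox models for death and progression, and rank tests on the markers that section 8(g) lists as primary outcomes. OS and progression are secondary (section 8(h)). The section gives no reason for the ten losses, no timing, and no count of losses in the rosuvastatin arm. It states no censoring rule for progression.

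**The concern.** For OS, a lost patient cannot both stay in the risk set until last seen alive and be absent from the analysis. A reader who follows one sentence gets a different analysis set from a reader who follows the other.

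The exclusion also reaches beyond OS. It depends on something that happened after allocation, it is reported for the control arm only, and it covers all tests, including those on the primary markers. The analysis then compares the rosuvastatin arm with the controls who stayed. If men who left differ in prognosis or marker course from those who stayed, part of any difference between arms reflects that selection. For the markers and for progression the exclusion contradicts no written rule. The defect there is the one-sided selection itself.

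**Working it through.** **Numbers allocated and analysed.** The inputs are 80 patients (section 8(i)), equal allocation and ten excluded controls (section 8(j)).

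- Allocated: 80/2 = 40 per arm. The protocol does not print 40; it follows from the two statements.
- Analysed: 40 rosuvastatin and 40 − 10 = 30 control, 70 in all, if no rosuvastatin patient was dropped.
- Loss: 10/40 = 25% of controls, 10/80 = 12.5% overall.

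**Direction of the effect on OS, measured against the plan's own rule.** The Kaplan-Meier estimate is the product over death times of (1 − d/n), with d deaths among n at risk. A patient described as lost to follow-up has no recorded death, so restoring the ten adds no d. It raises n at each death time up to their censoring date. Each factor therefore rises or stays the same. Excluding them can only lower the control curve or leave it unchanged.

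**Size, as an illustration.** The protocol gives no survival figures. Assume that 18 of the 30 retained controls are alive at 24 months and that the 12 deaths fall singly at months 2, 4, …, 24. Let all ten lost patients be censored at one time, after any death in that month:

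| Handling of the ten | Calculation | Two-year control survival |
| --- | --- | --- |
| Excluded | 18/30 | 60.0% |
| Censored at month 0 | 18/30 | 60.0% |
| Censored at month 6 | 37/40 × 18/27 | 61.7% |
| Censored at month 12 | 34/40 × 18/24 | 63.8% |
| Censored at month 18 | 31/40 × 18/21 | 66.4% |

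The choice between the two sentences moves control survival by 0 to about 6 points over this range, always upward when the ten are kept. Losses after month 18 would move it further; the limit is 28/40 = 70% if all ten were followed alive to month 24.

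**What neither rule resolves.** With 18 of 30 retained controls alive, survival among all 40 lies between 18/40 = 45% (all ten died) and 28/40 = 70% (all ten survived). This range describes the unknown outcomes of the ten. Censoring does not narrow it, because censoring is itself biased if loss is related to prognosis.

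**Is the imbalance in losses chance?** The answer depends on a count that the protocol does not give. Fisher's exact test of 10/40 control losses against k/40 rosuvastatin losses gives:

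| k | Two-sided p |
| --- | --- |
| 0 | 0.001 |
| 1 | 0.007 |
| 2 | 0.025 |
| 3 | 0.066 |
| 4 | 0.14 |

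**Power.** Section 8(a) requires 35 patients at 85% power and a 5% level, without an effect size and without saying whether 35 is per arm or in total. The figure therefore cannot be reproduced, only solved backwards. In the normal approximation for two means, two-sided, d = (1.960 + 1.036) × √(2/n). With n = 35 per arm, d = 0.716, and power is 89.3% at 40:40 and 84.3% at 40:30. With 35 in total (n = 17.5 per arm), d = 1.013, and power is 99.5% and 98.7%. Lost power is a minor part of the problem.

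**The case against.** Four arguments on the other side carry weight.

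- **The conflict is confined to OS.** This stands. The censoring sentence follows the OS definition and uses the date last known alive, so it cannot be read as a rule for progression or for the markers.
- **The consequence may be nil.** If all ten disappeared before the first control death, censoring and exclusion give the same control curve, as the month 0 row shows. The wording would still conflict, and the protocol does not say when they were lost.
- **The ten may have no usable data.** The protocol does not say that they had assays, later samples or a recorded date of last contact. Men with a baseline value only would add little on change. This limits what can be recovered, but it does not justify removing patients from OS when they have known survival time after diagnosis.
- **The sentence is an honest disclosure.** It is the only statement of attrition in the document and should be corrected, not deleted.

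A reader might also infer three stronger points that the protocol does not support. The first is that the rosuvastatin arm lost nobody: the text names only control losses, and with three rosuvastatin losses the imbalance would no longer reach 5%. The second is that the exclusion biases the result in favour of rosuvastatin: the one-way effect holds only against the plan's own censoring rule, while against the truth the sign depends on why the men left. The third is that the 45% to 70% range is the error caused by the exclusion: it is uncertainty that remains after censoring as well.

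**Conclusion.** The concern holds in this form. Section 8(j) gives two incompatible instructions for OS. Its exclusion sentence makes every between-arm comparison, primary markers included, a post-allocation completer comparison with a quarter of the controls removed. That fraction rests on 40 controls, derived from 80 patients and equal allocation.

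Under the assumed survival pattern, excluding instead of censoring lowers two-year control survival by 0 to about 6 points for losses up to month 18. The assumed 60% and the even spacing of deaths are illustrative, and the true size depends on the dates of loss. No size can be given for the markers from what the protocol states. The point should be settled before any comparison between arms is relied on, because it touches all of them and can be corrected without new patients.

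**What to change.** Keep the statement that ten controls were lost, and replace the exclusion clause with analysis of all patients as allocated. Specifically:

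- **OS:** include the ten and censor them at the date last known alive, as the section already states.
- **Progression:** state a matching censoring rule and apply it to both arms.
- **Markers:** include the ten at every time point where a value was obtained. The planned rank tests can stay.
- **Reporting:** give the number, timing and reasons of loss in both arms, including an explicit zero if the rosuvastatin arm had none.
- **Sensitivity:** keep the 70-patient analysis, labelled as such, and add best-case and worst-case bounds for two-year survival with the ten counted as all alive and all dead.

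The cost is a change of wording and a re-run using whatever last-contact dates and marker values exist for the ten. The protocol does not say which exist, so some retrieval from records may be needed. The result may become less favourable to rosuvastatin.
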